### Linezolid

Linezolid (LZD) is currently used as an effective rescue therapy in extensively drug resistant TB
^
6–
11
^. Its use is also established for the treatment of gram positive infections including pyogenic brain abscesses where patients receive 1200mg for four weeks
^
12
^. LZD is an attractive agent for the treatment of TBM due to its potent efficacy against
*Mycobacterium tuberculosis (M.tb)* as well as its excellent CNS penetration
^
12
^. Two published studies have investigated its potential role in TBM; the first, an observational study demonstrated favorable clinical outcomes and a non-significant difference in adverse events in children with drug sensitive TBM treated with LZD compared to control
^
13
^; the second, a retrospective cohort study of 33 adults with TBM found that the addition of LZD to a standard regimen led to more rapid improvement in CSF parameters, recovery of consciousness and reduction of fever
^
14
^.

LZD toxicity has however limited its use. The most common adverse events (AE) associated with LZD use in TB treatment are haematological toxicity (mainly dose-related) and peripheral neuropathy (mainly duration-dependent)
^
15
^. These are usually mild and are reversible with dose reduction or treatment interruption if identified early. In a systematic review, AE related to LZD use at doses > 600 mg/day occurred at a median of 252 days (IQR 120 – 540) of LZD exposure
^
16
^. In the
*NiX-TB* trial
^
17
^ where LZD was given at a total dose of 1200mg per day for 6 months, peripheral neuropathy occurred in 81% of cases with the majority of these occurring after 3 months of treatment. Median time to return to a normal or mild neuropathy score was 3 months. Myelosuppression was the second most common AE occurring in 48% of cases. Although these AE led to frequent treatment interruption (66% of cases had treatment interruption) all 109 participants completed 26 weeks of treatment. In the context of TBM, where morbidity and mortality are high, the risk-benefit of this potent antituberculous agent with good CNS penetration requires further evaluation in the context of a phase II safety trial.

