## Study design, recruitment and duration

LASER-TBM is a parallel group, randomised, multi-arm Phase 2A trial evaluating the safety of increased dose RIF plus LZD, with or without ASA, for the treatment of HIV-infected adults with TBM (
Figure 1). HIV-1 infected adults with newly-diagnosed TBM (up to n = 100) will be recruited from five public-sector hospitals across South Africa. Participants will be randomised in a 1.4:1:1 ratio across two experimental (n = 30 each) and one standard of care (n = 40) arms (
Figure 1). Relatively more participants will be randomised to the control group to account for the higher mortality anticipated in the standard of care arm. 

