## Statistical considerations

### Sample size

The total number of participants required for primary safety analysis is 100. This encompasses:

Arm 1 - control - (standard-of-care): 40

Arm 2 - experimental - (standard-of care + high dose rifampicin + linezolid): 30

Arm 3 - experimental - (standard-of care + high dose rifampicin + linezolid + aspirin): 30

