### Sample size justification

This phase IIA trial will focus on evaluating adverse events in the experimental arm relative to the standard of care arm. Solicited treatment related AE (
Table 1) plus deaths will be evaluated, and the Data Safety Monitoring Board (DSMB) will provide recommendations accordingly. The DSMB will review all safety events and approve the ongoing conduct of the trial. Analyses that will aid their decision-making will be based on several sources: 

First, a test of proportions will compare the AE rates between the standard-of-care arm and the experimental arms. Concerns about a worse safety profile will be flagged using a two-sided type I error rate of 0.1. Consider a scenario in which there are 10 out of 20 AE in the standard-of-care arm and 14 out of 20 in the experimental arms. This corresponds to a two- sided p-value of 0.053 using Boschloo’s test and would be reason for the DSMB to consider stopping the trial. 

Similarly, a Bayesian posterior probability (with an uninformative prior) of the probability that the AE rate in the experimental arm is worse than that in the control arm. This will provide an additional means of interpreting the relative results. If this probability is high, the DSMB may recommend stopping the study. For example, in the 10/20 and 14/20 scenario the posterior probability that the experimental arm has a worse rate of AEs is 94%. If the split was 10/20 versus 14/20, this probability would be 89%. The DSMB will be unblinded to safety data after every 15 patients recruited (5 per arm). At each point, absence of a significant safety signal (as outlined in the DSMB charter) will permit ongoing recruitment.

Although there is no power calculation to justify the primary outcome due to the complexity of multiple adverse events of special interests, it was felt that recruitment of up to 100 participants will allow sufficient numbers to permit calculations as detailed above and in doing so reveal a signal in terms of the safety of use of the three investigational products. Further detail is provided in the statistical analysis plan included as extended data
^
34
^.

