## Safety monitoring

### Safety oversight

Safety oversight will be under the direction of an independent DSMB. Comprised of independent internationally-recognised HIV-TB researchers and an independent statistician, the DSMB will meet after each 15 participants enrolled. The DSMB may also decide to convene an unscheduled review if warranted by safety or data quality concerns. The data for review will be prepared by an independent statistician.

The task of the DSMB will thus be to review study recruitment, data quality and trial drug safety and advise the sponsor of major safety issues and data quality issues. The DSMB may advise that trial enrolment should be paused or stopped entirely based on the decisions regarding the frequency and severity of solicited treatment related AE as outlined in
Table 1 (‘Solicited Treatment Related Adverse Events’).

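### The DSMB cohort of 15 recruits is described as five per arm, which contradicts the control-heavy 40/30/30 allocation; the interim adverse event proportions should also show how much follow-up lies behind them

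*Protocol article*

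**What the plan says.** All references are to the protocol article.

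- **Allocation.** Study design, recruitment and duration: "Participants will be randomised in a 1.4:1:1 ratio across two experimental (n = 30 each) and one standard of care (n = 40) arms". The next sentences give the reason: "Relatively more participants will be randomised to the control group to account for the higher mortality anticipated in the standard of care arm".
- **Arm sizes.** Sample size: "The total number of participants required for primary safety analysis is 100", listed as "Arm 1 - control - (standard-of-care): 40" and "Arm 2 - experimental - (standard-of care + high dose rifampicin + linezolid): 30", with 30 also in Arm 3. The abstract gives the same numbers.
- **DSMB reviews.** Sample size justification: "The DSMB will be unblinded to safety data after every 15 patients recruited (5 per arm"). Safety oversight repeats the trigger without a split by arm: "the DSMB will meet after each 15 participants enrolled".
- **What the DSMB sees.** Sample size justification names a test of proportions on adverse event (AE) rates and a Bayesian posterior probability. Absence of a significant signal, as defined in the DSMB charter, permits recruitment to go on.
- **Endpoint window.** Solicited AEs and death at 56 days.

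**The concern.** Two things do not fit together.

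First, a cohort of 15 with five in each arm can arise as a rule only under equal allocation. The design is deliberately unequal. A DSMB statistician who plans the reports from the Sample size justification section would expect different group sizes from one who works from the Study design section.

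Second, each review is triggered by a recruitment count, with no follow-up requirement stated in the article. The newest recruits have hardly entered the 56-day window. If they sit in the denominator of a crude proportion, the AE rate is understated in every arm. The continuation rule passes when no signal is seen, so the DSMB should be able to tell a low rate from short follow-up. The Linezolid section describes "peripheral neuropathy (mainly duration-dependent") as one of the drug's two most common toxicities in TB treatment, so time on treatment matters for at least one solicited event.

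**Working it through.** **1. Reproducing the stated split.** Expected number in an arm = N × (arm weight) ÷ (sum of weights).

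| N | 1:1:1 | 1.4:1:1 | 40:30:30 (= 4:3:3) |
|---|---|---|---|
| 15 | 5 / 5 / 5 | 6.18 / 4.41 / 4.41 | 6 / 4.5 / 4.5 |
| 60 | 20 / 20 / 20 | 24.7 / 17.6 / 17.6 | 24 / 18 / 18 |
| 90 | 30 / 30 / 30 | 37.1 / 26.5 / 26.5 | 36 / 27 / 27 |
| 100 | 33.3 / 33.3 / 33.3 | 41.2 / 29.4 / 29.4 | 40 / 30 / 30 |

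Only 1:1:1 reproduces five per arm. Under simple randomisation the chance of exactly 5/5/5 is 15!/(5!)³ × (p₁p₂p₃)⁵. This is 4.3% at 1.4:1:1 and 4.6% at 40:30:30.

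**2. The ratio itself.** 40 ÷ 30 = 1.33, not 1.4. Applied to 100, 1.4:1:1 misses the stated numbers by 1.2 in control and 0.6 in each experimental arm. That is rounding.

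**3. Follow-up at a look.** The article gives no accrual rate, so 2 to 8 per month is an assumption. Recruits arrive evenly, with a gap of 30.4375 ÷ rate days, and the look falls on the day of the Nth recruit. The i-th most recent recruit (i = 0, 1, …) has t = min(56, i × gap) days. With a true 56-day risk of 50%, the crude proportion seen is the mean of 1 − 0.5^((t/56)^k), where k = 1 is constant hazard and k = 3 an illustrative late hazard.

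Example at 5 per month, N = 15: the gap is 6.0875 days. The ten most recent recruits have 0 to 54.8 days, the other five have the full 56, and the mean at k = 1 is 34.7%.

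| Assumed recruits per month | Complete 56 days, of first 15 | Seen at 15, k = 1 | Seen at 15, k = 3 | Seen at 60, k = 1 |
|---|---|---|---|---|
| 2 | 11 | 43% | 40% | 48% |
| 3 | 9 | 40% | 35% | 47% |
| 5 | 5 | 35% | 27% | 46% |
| 8 | 0 | 27% | 13% | 44% |

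At 60 recruits and 5 per month, k = 3 gives 44%.

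**4. What understatement does to the comparison.** Arms are randomised concurrently, so incomplete windows fall on all of them alike. A simulation of a censored test against the crude one showed almost no gain in power. The gain is in reporting the AE rate correctly, not in a sharper test.

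**The case against.** The case against has real force, and most of it stands.

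- **The review rule as such.** A reader might infer that the cohort rule is wrong. The documents do not support that. The trigger is a total enrolment count, stated the same way in two sections, and enrolment-triggered safety reviews are ordinary practice. Removing the per-arm remark changes no look time.
- **The last ten recruits.** One might argue that six cohorts of 5/5/5 would force the last ten recruits all into control. That follows only if each cohort were forced to that split. Nothing says so, and randomisation runs from a pre-generated list.
- **The ratio.** One might count 1.4:1:1 against 40/30/30 as a further contradiction. Ratio and numbers stand in the same sentence, so the intention is plain.
- **Handling of short follow-up.** The article does not say that participants with incomplete windows count as event-free at a look. The x/n summary belongs to the final analysis. The signal definition and halting rules are left to the DSMB charter, which is not shown and may settle the denominator.
- **Other safeguards.** The scheduled review is not the only gate. AEs are assessed at every scheduled visit, unscheduled reviews are allowed, and the DSMB chair may recommend halting enrolment or dosing while the full board is consulted.
- **Late toxicity.** A reader might infer that look timing hides linezolid neuropathy. The Linezolid section reports that most neuropathy in the six-month 1200 mg trial came after 3 months, and that AEs above 600 mg/day arose at a median of 252 days. Most of that lies beyond the whole 56-day window, whatever the look times. The late hazard above has no source in the article.

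None of this rescues five per arm, which conflicts with figures printed in the same article.

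**Conclusion.** The per-arm remark is wrong. It implies 1:1:1 where the design is 40/30/30. The gap is about one participant per arm in a single cohort, and about 6 in control and 3 in each experimental arm by 90 recruits (36/27/27 against 30/30/30). This rests only on figures in the article.

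The follow-up point is an improvement and not a contradiction, and it falls away if the charter already covers it. It applies if the crude proportion is taken over everyone recruited. Its size rests on assumed accrual, a 50% risk and the hazard shape. Under constant hazard the rate seen is about 27% to 43% at the first look and 44% to 48% by 60 recruits. The article reports 52 enrolled, so the looks still to come (60, 75 and 90) are in the range where the understatement is smaller.

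**What to change.** 1. In Study design, recruitment and duration, state the allocation as 4:3:3, the ratio that gives 40/30/30. The randomisation list was generated before the trial began, so check the wording against it.
2. In Sample size justification, delete the five-per-arm remark. Keep the trigger at every 15 enrolled. Moving to multiples of 20, which divide evenly, would give five looks up to 100 instead of six and would delay the first, so it is not worth the tidier numbers.
3. Unless the charter already provides it, show next to the AE proportions the cumulative incidence of solicited AE or death by arm, censored at the data cut, with the number per arm past Day 28 and past Day 56. Because death is part of the composite, one minus the Kaplan-Meier estimate serves. For single AE types, treat death as a competing event.

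The cost is two wording corrections and one more table per DSMB report, from data already collected. No extra participants are needed, recruitment is not paused, and safety reviews stay as frequent as now.

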## Adverse events

### Assessment of AE

Study participants will be monitored and assessed for new AE at all scheduled study visits (as shown in
Table 4). At each visit trial staff will also assess the evolution and outcome of previously recorded AE. Safety monitoring of the study will be performed by a DSMB as described below.

### Severity of AE

All AE will be assessed for severity by study clinical investigators and graded as per the Division of AIDS (DAIDS) criteria
^
60
^. Each AE will be assigned a grade 1 to 5. For events not included in the protocol-defined grading systems, the following general definitions from grades 1 to 4 will be applied to classify event severity:

Changes in the severity of an AE should be documented to allow an assessment of the duration of the event at each level of intensity to be performed. AE characterised as intermittent require documentation of onset and duration of each episode.

### Solicited treatment related AE

Table 1 lists AE of special interest which are considered ‘solicited treatment related AE’ and therefore comprise primary safety endpoints of this study. These AE are reported regardless of causal relationship to study drugs. For each AE there is a specific objective measure incorporating the DAIDS grading criteria and other parameters of clinical significance. The management of each AE is summarised.

### Management of adverse events

Treatment must be discontinued for safety reasons if any clinical AE, laboratory abnormality, intercurrent illness, or other medical condition or situation occurs such that continued exposure to treatment would not be in the best interest of the participant. Management of solicited treatment related AE is summarised in
Table 1; detailed guidance for management of AE is provided in the manual of operating procedures.

## Safety monitoring

### Safety oversight

Safety oversight will be under the direction of an independent DSMB. Comprised of independent internationally-recognised HIV-TB researchers and an independent statistician, the DSMB will meet after each 15 participants enrolled. The DSMB may also decide to convene an unscheduled review if warranted by safety or data quality concerns. The data for review will be prepared by an independent statistician.

The task of the DSMB will thus be to review study recruitment, data quality and trial drug safety and advise the sponsor of major safety issues and data quality issues. The DSMB may advise that trial enrolment should be paused or stopped entirely based on the decisions regarding the frequency and severity of solicited treatment related AE as outlined in
Table 1 (‘Solicited Treatment Related Adverse Events’).

### Pausing and stopping rules

Halting rules for safety reasons will be detailed in the DSMB charter. In the event of serious safety concerns, the DSMB chair will consult the full DSMB by email or teleconference. Pending the DSMB response, the chair may use his/her discretion to recommend one or more if the following: Halt in study (arm) enrolment; halt in study (arm) dosing; provision of additional intervention; no action. After review, the DSMB will issue a recommendation to the trial steering committee to continue, modify (one or more arms) or terminate the trial.

## Data access and handling

### Source documents

Source data are original records of clinical findings, observations, or other activities necessary for the evaluation of the trial. Examples of these original documents and data records include, but are not limited to: hospital records, laboratory reports, and radiological images. Case report forms (CRF) may also be acceptable source documents. A complete list of source documents will be created prior to trial initiation.

The following individuals and groups will have access to study records:

- Members of the study team

- Relevant institutional review board (IRB)

- Regulatory agencies (South African Health Products Regulatory Authority - SAHPRA)

- Study Monitor

All site staff, the sponsor, and any sponsor representatives will preserve the confidentiality of all participants taking part in the study in accordance with ICH GCP, applicable South African national and local regulations and (to the extent applicable) the U.S. Health Insurance Portability and Accountability Act of 1996 (HIPAA). Subject to the requirement for source data verification by the study personnel by reference to the participant’s notes confidentiality of all participant identities will be maintained. Only participant study number and initials will be used on the CRF and in all study correspondence, as permitted. No material bearing a participant’s name will be kept on file by the sponsor. The written informed consent will contain a clause granting permission for review of the participants’ source data.

### Data collection, management and storage

Procedures to ensure data quality will be detailed in a data management plan. Data will be collected and captured onto hardcopy CRF on site and then entered into an electronic database. Clinical data will be entered onto paper CRF directly from the source documents on site. CRF will be cross-checked for accuracy, authenticity and completeness at the site by study staff; checks for consistency will be implemented at the data entry level on site and centrally after data entry.

The data will be managed and stored using a GCP-compliant web-based
REDCap® database custom-designed for the study. The REDCap® data entry and user permission structures provide auditing trails in line with international requirements. Access to the database is password controlled and will be limited to delegated trial staff with data entry and data management responsibilities.

### Publication of research findings

The definition of publication for this purpose is any public presentation of the data emerging from this study. All unpublished information given to the investigator by the sponsor shall not be published or disclosed to a third party other than to the responsible IRB, within the understanding of the confidentiality of their nature, without the prior written consent of the Sponsor. Results of this research will be submitted for publication as soon as feasible upon completion of the study in the form of a joint publication(s) between the sponsor and investigator(s), including site clinical and laboratory investigators, as appropriate

## Ethics

The trial has ethics approval from the University of Cape Town Human Research Ethics Committee (293/2018), Walter Sisulu University Human Research Committee (Ref 012/2019) and the South African Health Products Regulatory Authority (reference number 20180622). The trial is registered on the South African National Clinical Trials Register (DOH-27-0319-6230) and Pan African National Clinical Trials Register (PACTR201902921101705).

## Version control

Submitted version of the protocol: V6 (dated 11 May 2020).

## Protocol amendment policy

Any change to the protocol will be affected by means of a protocol amendment. The PI, HREC, and sponsor must agree on all amendments. No amendment will be implemented until approved by the relevant authorities and signed by all required parties. Exceptions to this are when the PI considers that the participant’s safety is compromised. No deviations from or changes to the protocol should be initiated without prior written approval from the IRB and regulatory authority. The PI, or designated site staff, is responsible for documenting and explaining any deviations from the protocol. Protocol deviations must be sent to the Sponsor and IRB in accordance with standard procedures.

## Study status

To date the study has enrolled 52 participants.

## Data availability

### Underlying data

No data are associated with this article.

### Extended data

Figshare: SPIRIT Checklist and Statistical Analysis Plan.
https://doi.org/10.6084/m9.figshare.14508561
^
34
^.

### Reporting guidelines

Figshare: SPIRIT checklist for ‘Study protocol for: Aa phase 2A trial of the safety and tolerability of increased dose rifampicin and adjunctive linezolid, with or without aspirin, for HIV-associated tuberculous meningitis [LASER-TBM]’.
https://doi.org/10.6084/m9.figshare.14508561
^
34
^.

Data are available under the terms of the
Creative Commons Attribution 4.0 International license (CC-BY 4.0).
